## Abstract

**Background:**

The best treatment option for end-stage renal disease is usually a transplant, preferably a live donor kidney transplant (LDKT). The most effective ways to educate kidney transplant candidates about the risks, benefits, and process of LDKT remain unknown.

**Methods/design:**

We report the protocol of the Enhancing Living Donor Kidney Transplant Education (ELITE) Study, a cluster randomized trial of an educational intervention to be implemented during initial transplant evaluation at a large, suburban U.S. transplant center. Five hundred potential transplant candidates are cluster randomized (by date of visit) to receive either: (1) standard-of-care (“usual”) transplant education, or (2) intensive education that is based upon the *Explore Transplant* series of educational materials. Intensive transplant education includes viewing an educational video about LDKT, receiving print education, and meeting with a transplant educator. The primary outcome consists of knowledge of the benefits, risks, and process of LDKT, assessed one week after the transplant evaluation. As a secondary outcome, knowledge and understanding of LDKT are assessed 3 months after the evaluation. Additional secondary outcomes, assessed one week and 3 months after the evaluation, include readiness, self-efficacy, and decisional balance regarding transplant and LDKT, with differences assessed by race. Although the unit of randomization is the date of the transplant evaluation visit, the unit of analysis will be the individual potential transplant candidate.

**Discussion:**

The ELITE Study will help to determine how education in a transplant center can best be designed to help Black and non-Black patients learn about the option of LDKT.

**Trial registration:**

Clinicaltrials.gov number NCT01261910

## Background

For patients with end-stage renal disease (ESRD), a kidney transplant from a living donor is usually the best treatment option. Living donor kidney transplants (LDKTs) and deceased donor kidney transplants (DDKTs) both improve ESRD patients’ survival and quality of life [1-4]. LDKT, however, offers several potential advantages compared to DDKT. LDKT allows transplant candidates to bypass the long DDKT waitlist, minimizes (and enables avoidance of) chronic dialysis and its associated morbidities [5], can be scheduled for a time convenient for the transplant recipient and living donor, and facilitates transplant among sensitized transplant candidates (who are often unable to otherwise receive a transplant) [6,7]. Furthermore, LDKT offers substantially better patient and allograft outcomes than DDKT [8]. For many patients, LDKT provides the only alternative to death on dialysis, while awaiting a DDKT [9,10].

Unfortunately, despite the many advantages of LDKT, Blacks with ESRD are less likely to receive LDKTs, compared to non-Blacks [11-13]. In 2011, Blacks made up 33.2% of the waiting list for DDKTs and received 32.2% of all DDKTs but received only 14.0% of all LDKTs [14]. This striking racial disparity stems from multiple factors and barriers [15,16]. One such barrier may be a need for more education and knowledge of LDKT and living donation, given the desire by Blacks (and non-Blacks) for such education and knowledge [17-19].

In addition to its advantages, LDKT has short-term and possibly long-term risks for living donors [20]. The short-term, peri-operative risks of donor nephrectomy (e.g. bleeding, infections, pneumothorax, and venous thromboembolism) resemble the risks of similar operations. Peri-operative death is very rare, occurring in approximately 0.03% of nephrectomies [21-23]. Long-term, living kidney donors may have increased risks of hypertension [24], proteinuria [25], and chronic kidney disease (CKD) [26,27]. These risks may be increased among donors who are Black, versus non-Black [23,26,27]. Despite these possible risks, living kidney donors appear to have the same rates of death and ESRD as the general population [10,23,28-30].

Given the substantial benefits of LDKT for the recipient and the possible long-term risks of nephrectomy for the living donor, kidney transplant candidates (and their living donors) should make informed choices regarding whether to pursue LDKT. Better education may increase CKD patients’ knowledge of LDKT. Among CKD patients, increased knowledge of LDKT has been associated with increased comfort in discussing LDKT with others and decreased concerns about live kidney donation [17].

The best source for accurate information about the process, risks, and benefits of LDKT is likely the local transplant center [31]. In the U.S., the Centers for Medicare and Medicaid Services has currently approved approximately 235 centers to perform kidney transplants [32]. Approved transplant centers must educate and inform patients about transplantation [33], but these centers vary greatly in how they deliver this education [34]. Each center educates patients using its own combination of print materials, videos, and group or one-on-one discussions with transplant personnel [34]. The best ways to provide education about LDKT remain unknown, so studies of potentially effective and replicable approaches to LDKT education are needed.

Therefore, we describe the protocol for the Enhancing Living Donor Kidney Transplant Education (ELITE) study, a cluster randomized clinical trial designed to test the impact of an educational intervention upon potential transplant candidates’ knowledge of LDKT. As mandated by the funding source, the federal Health Resources and Services Administration (HRSA), and grant program, the primary outcome of this study is knowledge of the benefits, risks, and process of live donor kidney transplant, rather than rates of actual LDKT [35].

## Methods/design

### Study design summary

The ELITE study is a single-center, cluster randomized [36,37], parallel group clinical trial designed to test the effectiveness of an educational intervention [38] upon transplant candidates’ knowledge of LDKT (see Figure 1 for flow diagram and Additional file 1 for CONSORT 2010 checklist of information to include when reporting a cluster randomised trial). All study procedures were approved by the Institutional Review Boards at both Saint Barnabas Medical Center (SBMC, protocol number 2009–53) and the University of Medicine and Dentistry of New Jersey (protocol number 0120100096).

**Figure 1 F1:**
[figure not shown]
Flow diagram of study activities.

### Target population, setting, and inclusion/exclusion criteria

The targeted patient population consists of Black and non-Black persons with CKD who underwent evaluation for kidney transplant (potential transplant candidates) at Saint Barnabas Medical Center, a suburban transplant center and academic teaching hospital in Livingston, New Jersey, in the northeastern United States. We use the term “potential transplant candidates” to describe CKD patients who are referred for transplant and appear for evaluation by the transplant center. “Transplant candidates”, also known as “listed” or “actual” transplant candidates, are potential transplant candidates who are deemed suitable for transplant, made active on the waiting list for a DDKT, and able to receive a LDKT if they have a living donor. During the two years prior to the ELITE study, Saint Barnabas Medical Center evaluated approximately 700 potential transplant candidates per year.

Persons are eligible for the ELITE study if they meet the following inclusion criteria: (1) appear for initial kidney transplant evaluation at Saint Barnabas Medical Center; (2) are 18 years of age or older; (3) are able to provide informed consent; and (4) are able to speak, hear, and understand English. We exclude persons from the ELITE study if they: (1) have significant neurocognitive disability that would prevent participants from understanding the study or completing the questionnaires; (2) are unable to speak, hear, and understand English; (3) are visually impaired and unable to complete self-administered case report form; and (4) have a self-described unwillingness or inability to complete phone interviews.

### Study aims

Our primary aim is to determine the effects of an educational intervention (intensive transplant education), versus standard-of-care (usual) transplant education, upon transplant candidates’ knowledge of the benefits, risks, and process of LDKT, assessed one week after transplant evaluation.

As secondary aims, this study will also determine differences in readiness, self-efficacy, and decisional balance regarding transplant at one week after transplant evaluation, between patients who receive intensive, versus usual, transplant education. The study will also examine how knowledge, readiness, self-efficacy, and decisional balance change between one week and three months, in patients who receive intensive, versus usual, transplant education. Finally, the study will also determine how known barriers to LDKT, including Black race, less prior transplant education, and lower health literacy, act alone and in combination with the educational interventions to affect patients’ level of knowledge at one week and three months.

### Randomization

#### ***Randomization procedures and rationale for cluster randomization***

All the potential transplant candidates on a given evaluation day are cluster randomized to either standard-of-care transplant education (“usual” care or control, Arm 1) or intensive transplant education (experimental, Arm 2). At Saint Barnabas Medical Center, transplant education generally occurs thrice weekly, on Tuesdays, Wednesdays, and Fridays. Immediately before each week’s evaluations begin, we randomize each week’s evaluation days, using a computer-generated random number. Therefore, the unit of randomization will be the date of the transplant evaluation. As with most educational interventions, we are unable to blind or mask study personnel and participants regarding treatment allocation groups (usual care vs. intensive education). The study arm is unknown, however, at the time the potential transplant candidates scheduled their evaluations.

We chose cluster randomization to minimize contamination between study arms [39] as well as for practical administrative reasons. If we randomize at the level of the individual patient (potential transplant candidate), then on a given evaluation date, some potential transplant candidates will receive usual care (standard-of-care education), while others will receive intensive education (the intervention). Because potential candidates often talk and share information with each other throughout the evaluation day, randomization at the level of the individual patient will likely lead to significant contamination between study arms. Cluster randomization minimizes such contamination. In addition, by assigning all patients on a given date to receive the same education (usual or intensive), cluster randomization facilitates coordination of the transplant evaluation with performance of this research trial. Although the unit of randomization is the date of the transplant evaluation, the unit of analysis will be the individual potential transplant candidate.

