### Standard-of-care (usual) transplant education (Arm 1)

During their transplant evaluation day, potential transplant candidates randomized to standard-of-care (usual) initial education will receive the standard transplant education and evaluation provided by SBMC. Family and friends are encouraged to accompany the patient to the evaluation. First, patients and their guests listen to and view a 90-minute slide presentation given by one of our trained transplant nurse coordinators. The presentation reviews:

• treatment options for chronic kidney disease, including LDKT and DDKT;

• the kidney transplant evaluation process;

• how the deceased donor waiting list works;

• the types of LDKTs and DDKTs. These slides succinctly review the benefits of LDKT, the workup of potential living donors, the types of living kidney donors, and alternative programs for LDKT;

• potential medical and psychosocial benefits and risks of kidney transplantation

• what to expect with the surgical procedure; and

• patients’ rights and responsibilities.

These topics must be included in the educational information provided to potential transplant candidates, as mandated by the Centers for Medicare and Medicaid Services [33].

After the presentation, potential transplant candidates are evaluated in private offices by members of the transplant team, including the transplant nurse coordinator, social worker, nephrologist, dietician, and financial coordinator. Potential transplant candidates meet separately with each transplant team member in a varying, unsystematic order, based on the availability of the team members. The research nurse or assistant also meets privately with each potential transplant candidate. Because the order in which potential transplant candidates meet with team members is unsystematic, the meeting between the research staff and the patient may occur at any point during the evaluation. The research staff member determines the patient’s eligibility for the study, obtains informed consent, and administers the initial questionnaires. The research nurse or assistant also sets an appointment date and time, at approximately one week after the transplant evaluation, for phone administration of follow-up questionnaires measuring knowledge and other outcomes.

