### Intensive transplant education (experimental, Arm 2)

Potential transplant candidates who are cluster-randomized to intensive initial education (Arm 2) undergo the same education and evaluations as candidates in the usual education group. Additionally, study participants in the intensive education arm also undergo an intervention designed to increase knowledge of LDKT. This intervention is directed by the research nurse or assistant, who functions as a Transplant Educator. The intervention is based upon materials from the *Explore Transplant* series of kidney transplant education materials. When implemented in dialysis units, *Explore Transplant* has been shown to increase dialysis patients’ pursuit of DDKT and LDKT [40]. However, *Explore Transplant* has yet to be tested at a transplant center.

Our educational intervention consists of two parts, both implemented on the day of the transplant evaluation. First, study participants (together with any friends and family who accompanied them) view a 25-minute video, entitled “The experiences of living kidney donors”, from the *Explore Transplant* series of kidney transplant education materials [41,42]. This video, intended for potential transplant candidates, discusses how living donors came to their decision to donate; donors’ motivations and what they learned; facts about the donor evaluation, surgery, and recovery; risks to the living donors; and life after donation. The learning objectives of the video are to enable the viewer to understand the evaluation, surgery, and recovery process of living donors; learn possible risks that living donors face and how often these risks occur; learn the advantage of living donor kidneys versus deceased donor kidneys; and learn ways family member and friends can provide support to transplant candidates. The video features the stories of actual living kidney donors and presents accurate medical facts about LDKT, presented by medical professionals.

Second, after viewing the video, the study participants meet privately with the trained Transplant Educator for a fifteen-minute meeting to:

• Answer any questions that patients may have had, based upon what they saw in the video;

• Explore with patients their reasons for wanting a kidney transplant;

• Explore with patients their current situation with CKD/ESRD;

• Examine how the patients’ CKD/ESRD affects their family and friends;

• Answer any questions or concerns about transplant that the patient has;

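### Eligibility and consent are settled after the day's arm is fixed, by unmasked staff in the role that delivers the intervention, so recruitment could differ between arms

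*Protocol article*

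**What the plan says.** All references are to the protocol article.

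- **When the arm is set.** Under *Randomization procedures and rationale for cluster randomization*: "Immediately before each week’s evaluations begin, we randomize each week’s evaluation days, using a computer-generated random number". The same section says that neither study personnel nor participants can be masked, and then gives the one concealment it claims: "The study arm is unknown, however, at the time the potential transplant candidates scheduled their evaluations".
- **Who recruits.** Under *Standard-of-care (usual) transplant education (Arm 1)*: "The research staff member determines the patient’s eligibility for the study, obtains informed consent, and administers the initial questionnaires". On timing, "the meeting between the research staff and the patient may occur at any point during the evaluation". The Arm 2 section says that those candidates undergo the same evaluations.
- **Who delivers the intervention.** Under *Intensive transplant education (experimental, Arm 2)*: "This intervention is directed by the research nurse or assistant, who functions as a Transplant Educator".
- **Criteria open to influence.** Under *Target population, setting, and inclusion/exclusion criteria*, persons are excluded if they "have significant neurocognitive disability that would prevent participants from understanding the study or completing the questionnaires" or "have a self-described unwillingness or inability to complete phone interviews".
- **What is measured and analysed.** *Measurement timepoints* says that knowledge cannot be measured before the education starts, and that the telephone assessors are blinded and do not recruit. *Statistical analysis* makes the per-protocol analysis primary and the intent-to-treat analysis, with multiple imputation, a sensitivity analysis of enrolled participants. *Primary analysis* adjusts for baseline characteristics that turn out unequal.

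**The concern.** In a cluster trial, randomising the clusters protects the comparison only if entry to the analysis does not depend on the arm. Here the cluster is a day, the arm of that day already exists, and patients are enrolled one at a time by someone who can know it. The intensive arm also asks more of the patient: a 25-minute video and a fifteen-minute meeting, 40 minutes in all. If that knowledge or burden changes who is excluded or who agrees, the enrolled groups differ before any education has its effect.

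The primary outcome is a knowledge score at one week. Patients more willing to sit through extra education may also know more about transplant, or less. Without a knowledge score at entry, such a difference cannot be examined directly, and part of the estimated effect could be selection.

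**Working it through.** **1. Order of events.** The weekly draw comes first. Screening, consent and the initial questionnaires follow on the evaluation day. The article does not state outright that the recruiter knows the arm at consent. It follows in practice, because unmasked staff in that role must run the video and meeting the same day.

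**2. Whether the stated safeguards reach this step.**

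| Safeguard | What it protects | Enrolment from a given day? |
|---|---|---|
| Arm unknown at scheduling | which patients fall on which day | no |
| Blinded telephone assessors | measurement of the outcome | no |
| Adjustment for unequal baseline variables | measured differences among those enrolled | in part |
| Intent-to-treat with multiple imputation | missing data among those enrolled | no |

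**3. Room for selection.** Inputs: about 700 evaluations a year, three evaluation days a week, about 100 days and 250 patients per arm.

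- Days per year: 3 × 52 = 156. Evaluated per day: 700/156 = 4.49.
- Over 200 days: 200 × 4.49 ≈ 897 evaluated. Enrolled share: 500/897 ≈ 56%, so about 44% are not enrolled.

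This assumes that the earlier evaluation rate holds and that three days run every week. The 44% is an upper limit on discretionary loss, since it includes patients who are plainly ineligible. If 500 is the number still present at one week, enrolment is higher and the gap smaller.

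**4. Size of a possible bias.** The plan gives no recruitment rates by arm, so it has no figure to reproduce here. Assume that willingness to enrol is a standard normal trait correlated r with knowledge, and that a fraction p consents. The mean knowledge of those who consent is then shifted by r·φ(z)/p SD, where z is the cut-off exceeded by a fraction p. The bias is

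r × [φ(z_b)/b − φ(z_a)/a],

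with a = 0.60 (usual, assumed) and b the assumed consent under intensive education. The ratios φ(z)/p are 0.644 at 0.60, 0.720 at 0.55, 0.798 at 0.50 and 0.880 at 0.45.

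| Consent, usual vs intensive | r = 0.3 | r = 0.5 |
|---|---|---|
| 60% vs 55% | 0.023 SD | 0.038 SD |
| 60% vs 50% | 0.046 SD | 0.077 SD |
| 60% vs 45% | 0.071 SD | 0.118 SD |

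With equal consent and equal exclusions the bias is zero. With a positive r and lower consent under intensive education it favours the intervention; reversing either sign reverses it.

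**5. Scale.** The plan's power statement (at least 95% for a 10–20% difference) gives no SD and cannot be reproduced exactly. With its ICC of 0.4 and 2.5 patients per day, the design effect is 1 + 1.5 × 0.4 = 1.6 and the effective size is 250/1.6 = 156 per arm. The standard error is √(2/156.25) = 0.113 SD. With a two-sided 5% level assumed, 95% power corresponds to (1.960 + 1.645) × 0.113 = 0.41 SD. That number is back-calculated and is not the plan's own. With no true effect, a shift of 0.023 SD would raise the rejection rate from 5% to about 5.5%, 0.071 SD to about 10%, and 0.118 SD to about 18%.

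**The case against.** The strongest case against has four parts.

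- **Staff meet everyone.** The Arm 1 section says that the research nurse or assistant meets privately with each candidate. A reader might infer that staff can choose whom to approach. The text does not support that. What remains open is who is judged eligible and who agrees.
- **The criteria are mostly objective.** Age, English and vision leave little discretion, and reluctance about phone interviews is self-described, so staff do not judge it. Only neurocognitive disability clearly calls for staff judgement. This narrows the route through exclusion but leaves the route through consent.
- **Imbalance can partly be seen.** A reader might infer that a recruitment difference would be invisible and beyond correction. That goes too far. Health literacy, prior education, earlier actions to learn about transplant, and demographic and medical characteristics are collected on the day, compared by arm and adjusted for. The protocol itself treats several of these as related to knowledge. They remain proxies.
- **Scripts and logs belong in the full protocol.** An article may leave such forms out, and their absence alone would be no finding. But the article itself fixes the order of events, the lack of masking and the shared role, and claims concealment only at scheduling.

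The assumed consent rates have no source in the document, and a smaller or zero gap fits it equally well.

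**Conclusion.** The concern stands as a risk built into the recruitment sequence: the arm is fixed first, and unmasked staff in the intervention role then determine eligibility and obtain consent. None of the described safeguards conceals the arm at that step, and planned covariate adjustment answers it only in part.

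The documents do not show that bias has occurred, nor how large it would be. The range of about 0.02 to 0.12 SD rests wholly on the assumed consent rates and correlations, before any adjustment. At the low end it would hardly matter; at the high end it would materially inflate the false-positive rate. The change is worth making because it is cheap and because, without recruitment counts by arm, a reader of the results could not tell which end applies.

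**What to change.** 1. Use one arm-neutral eligibility checklist and one consent script that describes both arms, on every evaluation day.
2. Tell the patient the day's arm only after eligibility, consent and the initial questionnaires are complete.
3. Log the numbers evaluated, eligible and consented for each day, with reasons for exclusion.
4. Report exclusion and consent rates by arm alongside the primary result.

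Drawing the arm each morning instead of weekly would not solve the problem, because the arm would still be fixed before that day's consents.

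The cost is slightly more paperwork with existing staff, and cluster randomisation by day is unchanged. The limit is that staff will still know the arm on intensive days, and candidates who talk to one another may learn it. The bias is therefore reduced and made visible, not removed.
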